### Measures and Data Collection

#### Overview

A range of data measures has been developed and selected to define individual, caregiver, and TAND severity characteristics at baseline, during longitudinal data collection, and in the pilot well-being intervention. Measures were selected if they were freely available, comprehensive, and had good psychometric properties.

#### Measures and Data Collection Methods (Aims 1 and 2)

The measures for aims 1 and 2 include demographic information, TSC characteristics, TAND severity, TAND interventions, and information about well-being. All of these measures will be collected using the TAND Toolkit app, adapted for longitudinal data collection and accessibility via various electronic devices (such as smartphones, tablets, or desktop computers). Table 3 summarizes the data measures, app sections, time points at which each measure will be completed, the estimated length of time measures will take to complete, and who the measures capture information about. There will be 5 data collection time points over a 12-month period, with 3-month intervals.

**Table 3 table3:** Data collected using the tuberous sclerosis complex (TSC)–associated neuropsychiatric disorders (TAND) Toolkit app for aims 1 and 2.

Data measures and the type of information collected			TAND Toolkit app section		Data collection time points		Estimated time to complete	Who the measures are completed about
**Demographic information**								
	Age Education level and type Family living situation Employment and income	My TSC Family		1		5 min		Individuals with TSC and the caregiver (if relevant)
**TSC characteristics (My TSC Story)**								
	Age diagnosed First concerns Current physical symptoms in each body system Genetic testing and genotype Seizure characteristics Treatments	My TSC Story		1-5		15 min		Individuals with TSC
**TAND severity (TAND-SQ^a^)**								
	Developmental milestones Behavioral difficulties Psychiatric diagnoses Intellectual ability Scholastic difficulties Neuropsychological difficulties Psychosocial difficulties Priorities, strategies, and strengths	My TAND Checklists		1-5		30 min		Individuals with TSC (and question 8.2 for the caregiver, if relevant)
**TAND interventions**								
	Type of intervention (medications, psychological/behavioral/talking, educational, social, caregiver or family training, or other) Which cluster it was targeting What difference it made	My TAND Interventions		1-5		10 min		Individuals with TSC
**Well-being**								
	Care/caregiving burden Brief Resilience Scale [82] Patient Health Questionnaire-9 [64] Generalized Anxiety Disorder 7-item scale [65] World Health Organization-5 Well-Being Index [83] Overall well-being rating	My Well-being		1-5		10 min		Individuals with TSC (only self-report); caregivers (only self-report)

^a^TAND-SQ: self-report quantified TAND checklist.

To support longitudinal data collection, the app includes built-in features to encourage retention. There will be automated “reminders” for new data collection time points through in-app notifications and emails to participants. Efforts have been made to ensure each data collection time point is not too time-consuming. Data collection for time point 1 will take approximately 60-70 minutes. At time points 2-5 (T_2_-T_5_), the total data collection time should be faster as several items within the My TSC Story, My TAND Checklist, and My TAND Interventions sections will be prepopulated, thus only requiring updates to be completed. We anticipate data collection at time points T_2_-T_5_ to take 30-40 minutes. We will include visual summaries of the data entered by participants, which will allow them to view changes in their TAND severity over time. These are intended to encourage participants to return to the app for data entry at the subsequent time points. The app will generate PDF summaries of information provided by participants that can be downloaded and shared with health care teams. The app contains the TAND toolkit, developed as part of the TANDem-1 project [20], containing a range of evidence-informed suggestions for what additional clinical help to seek and what can be tried at home for symptoms across all TAND clusters. Access to the TAND toolkit is also considered a retention strategy.

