### From TANDem-1 to TANDem-2: Closing the Gap to TAND Interventions Through Participatory Research

In TANDem-1, the TAND consortium (an international group of TSC clinical research and lived experts with a focus on TAND research [19]) converted the TAND-L to a self-report quantified checklist (self-report quantified TAND checklist [TAND-SQ]) that individuals with TSC or their caregivers could use to document and quantify TAND difficulties themselves [20]. The TAND-SQ was feasible and acceptable to the TSC community, particularly families, who are the primary intended respondents for the TAND-SQ [20]. In the TAND-SQ, a 0-10 severity rating was added to all TAND cluster items, allowing the quantification of TAND difficulties experienced over the past month. Table 1 summarizes the range of TAND severity scores that can be derived using the severity ratings from the TAND-SQ, as proposed by the TAND consortium [21]: an individual item severity score, a mean cluster severity score (CSS_mean_), a maximum cluster severity score, a mean total TAND severity score (TTSS_mean_), and a maximum total TAND severity score (TTSS_max_). The CSS_mean_ has been found to be internally consistent and significantly related to relevant clinical diagnoses and standardized behavioral measures. The TTSS_mean_ has also been found to be a valid indicator of overall functioning and behavior [21].

**Table 1 table1:** Tuberous sclerosis complex–associated neuropsychiatric disorders (TAND) severity scores that can be derived from the self-report quantified TAND checklist.

Score name	Description	Maximum score	Proposed purpose
Individual item severity score (IISS)	TAND severity score of an individual item (eg, sleep)	10	Most useful to track an individual TAND manifestation of interest
Mean cluster severity score (CSS_mean_)	The arithmetic mean score of a specific TAND cluster (eg, autism-like cluster)	10	Most useful to compare one mean cluster score to another with the same maximum score of 10
Maximum cluster severity score (CSS_max_)	The arithmetic sum of all severity scores within a specific TAND cluster (eg, all 4 items in the scholastic cluster)	Maximum scores vary by cluster, given the varying number of items per cluster	Most useful to track the total severity of a specific cluster
Mean total TAND severity score (TTSS_mean_)	The arithmetic mean of all severity scores across all TAND clusters	10	Most useful to track or examine overall TAND severity

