To begin exploring this question, we performed preliminary analyses of TAND severity over time using data from the TAND-SQ validation study [21], which included 21 repeat completions of the TAND-SQ. The checklists were completed with a mean age of 9.7 (SD 3.63; range 4-15) months apart. A total of 18 checklists were completed by caregivers of individuals with TSC reporting on their child (aged <18 years, n=12), or adult (aged >18 years, n=6) dependents, and 3 were individuals with TSC reporting for themselves. For analysis of change in TTSS_max_, we used the time of the second observation as integer months since the first observation (Table 1). Linear mixed-effects model fit by restricted maximum likelihood, including subject-specific random effects, showed that the mean TTSS_max_ was 100.5 (SD 64.2) at baseline, and that it changed by –1.05 units per month, equating to a 1% decline per month (10 units over 10 months or 12 units over 12 months). These findings therefore showed a “group-based” finding of gradual decline in the TTSS_max_ over time (Figure 1A), suggesting improvement in TAND severity over time. To explore the possibility of latent classes of change trajectories, we set a 10-unit change as a clinical marker of meaningful change (given that 10 units is the total of 1 severity quantification range per item). We grouped the 21 sets of observations into 3 groups based on whether trends between the 2 time points showed a decrease of >10 units, stayed within 10 units, or showed an increase of >10 units. We then regressed the TTSS_max_ per month, allowing for interaction with the 3 classes (stable, increasing, and decreasing). Results (Figure 1B) showed that 5 (24%) participants remained within 10 units from a relatively low baseline (T_0_ mean TTSS_max_ 52.6, SD 46.6), 5 (24%) participants had scores that increased by >10 units from a higher baseline (T_0_ mean TTSS_max_ 77.4, SD 70.0), and 11 (52%) participants had scores that reduced by >10 units from a high baseline (T_0_ mean TTSS_max_ 133.1, SD 63.2). These preliminary findings support the hypothesis of potential differential trajectories in TAND severity over time.

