#### Aim 1: Examine the Longitudinal Trajectories of TAND Severity and Their Predictors

We hypothesize that longitudinal analysis of TAND severity data will identify at least 3 differential trajectories (“stable,” “worsening,” “improving”), and that trajectory membership will have differential predictors. To test this hypothesis, we will use an accelerated longitudinal design to collect longitudinal data from 500 families across 5 time points with 3-month intervals over a 12-month period.

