### Data Analysis

#### Statistical Analysis Plan (Aim 1)

TAND severity will be quantified using the CSS_mean_ for each cluster and the TTSS_mean_/TTSS_max_ for overall TAND severity. These will be used to identify latent TAND severity trajectories using latent class mixed effect modeling [84]. The number of classes will be chosen based on statistical measures of model fit, the stability of the latent profiles, and the group sizes. Multinomial regression modeling [84] will be used to investigate the association of potential subject-specific covariates with the identified latent classes (predictors of TAND severity trajectories). All analyses will be done using R software (R Foundation for Statistical Computing) [85].

Power calculations are based on the estimation of the time trajectory and comparing different latent trajectories. Based on the data from the preliminary data analyses described earlier of 21 repeat TAND-SQs (42 observations), the power calculations were made in 2 ways. First, based on simulations [86] using a single slope (mean profile), power for sample sizes of n=500 and n=300 was calculated at a slope of -1.05% (power=100%/100%) and at –0.5% (power=97%/81%). Second, simulations were generated for n=500 and n=300 using a 3-trajectory solution with change in trajectories set at +1%, 0%, –1% (power=100%/100%), +0.5%, 0%, –0.5% (power=84%/72%), and 0%, +0.5%, +1% (power=86%/83%). Power calculations allowing for 3 different estimated baseline values of TTSS_max_ (75, 100, and 125) in addition to differing slopes for trajectories, show for n=500, 100% power (with 1% change in trajectories) and 93% power (with 0.5% change in trajectories). A sample size of n=300 using similar power calculations shows 100% power for 1% and 77% power for 0.5% differences in trajectory slopes.

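### Pre-filling of TAND checklist items at T2-T5 is not limited to history items, so untouched severity ratings could be stored as new measurements and pass for stability

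*Protocol article*

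**What the plan says.** The rule stands in the protocol article, Measures and Data Collection Methods (Aims 1 and 2), in the text after Table 3. To shorten the later waves, "several items within the My TSC Story, My TAND Checklist, and My TAND Interventions sections will be prepopulated, thus only requiring updates to be completed". The same paragraph adds, as a retention feature, "visual summaries of the data entered by participants, which will allow them to view changes in their TAND severity over time".

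Table 3 identifies My TAND Checklists as the TAND-SQ section, completed at time points 1-5. Its content is mixed: "Developmental milestones Behavioral difficulties Psychiatric diagnoses Intellectual ability Scholastic difficulties Neuropsychological difficulties Psychosocial difficulties", followed by priorities, strategies and strengths. Question 8.2 on the caregiver sits in the same section.

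The introduction (From TANDem-1 to TANDem-2) explains that "a 0-10 severity rating was added to all TAND cluster items, allowing the quantification of TAND difficulties experienced over the past month". Those ratings are the outcome. Under Statistical Analysis Plan (Aim 1), "TAND severity will be quantified using the CSS_mean_ for each cluster and the TTSS_mean_/TTSS_max_ for overall TAND severity". The Aim 1 hypothesis is that "longitudinal analysis of TAND severity data will identify at least 3 differential trajectories", one of them stable.

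The article does not say which checklist items are pre-filled, whether the 0-10 ratings start blank, or whether an unchanged value must be confirmed.

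**The concern.** A rating of the past month has to be made afresh at each wave. If the field opens with the answer from three months before and only changes need entering, leaving it alone can mean two things: the respondent judged it unchanged, or the respondent did not look. The database would hold the same number in both cases.

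This matters more here than in most designs, because stability is itself one of the hypothesised results. Carried-over values imitate the stable class, pull the slopes of changing participants toward zero, and make errors at successive waves share a component. No later analysis can separate true stability from a skipped item unless untouched values were logged, and a missed past-month rating cannot be collected afterwards.

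For Aim 2 the exposure is narrower. The baseline mediation model uses data collected before any pre-filling, and the My Well-being scales are not among the sections listed. Question 8.2 at later waves lies inside the checklist, so if it is pre-filled and used in the sequential models, mediator and outcome could both carry old values.

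**Working it through.** **Step 1. Do the stated completion times show what is pre-filled?** Inputs are from Table 3 and the text after it.
- Time point 1: 5 + 15 + 30 + 10 + 10 = 70 min, matching the upper end of the stated 60-70 min.
- Later waves without demographics: 70 - 5 = 65 min. The stated target is 30-40 min, so 25-35 min must be saved.
- Well-being (10 min) is not listed as pre-filled. My TSC Story and My TAND Interventions can save at most 15 + 10 = 25 min.
- The 30-min checklist must therefore save at least 0-10 min, and more if the other two sections still take time.

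Pre-filling history items alone could supply that saving; so could pre-filling ratings. The times do not settle the question.

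**Step 2. What would happen to the mean slope if ratings were pre-filled?** The share q left untouched at each wave is an assumption; the document gives no value. The calculation treats every untouched rating as out of date, which overstates the effect where nothing had changed. With the true value T_k = k at waves k = 0, 1, 2, 3, 4 (months 0, 3, 6, 9, 12), the expected recorded value is

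o_k = (1 - q) k + q o_(k-1), with o_0 = 0.

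The least-squares slope relative to the truth is (-2 o_0 - o_1 + o_3 + 2 o_4) / 10.
- q = 0.25: o = 0, 0.75, 1.6875, 2.6719, 3.6680. Ratio = (-0.75 + 2.6719 + 7.3359) / 10 = 0.926.
- q = 0.5: o = 0, 0.5, 1.25, 2.125, 3.0625. Ratio = (-0.5 + 2.125 + 6.125) / 10 = 0.775.

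If instead a share f of participants never updates anything, the mean slope is multiplied by 1 - f, and those participants look exactly flat. That is the direct route to an inflated stable class.

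**Step 3. In outcome units.** The preliminary slope in the introduction is -1.05 TTSS_max units per month, or -1.05 x 12 = -12.6 over the study. At q = 0.5 the recorded change is -1.05 x 3 x 3.0625 = -9.65. For the preliminary data the authors wrote that "we set a 10-unit change as a clinical marker of meaningful change". An average decline of 12.6 lies outside that band and 9.65 lies inside it. This is only a yardstick: the planned analysis is a latent class mixed model, not the 10-unit rule.

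**Step 4. Can this be turned into power?** Not reliably. The stated power for a 0.5% slope is 97% (n=500) and 81% (n=300). The article gives no residual or random-slope SD, so these figures cannot be reproduced from its inputs, and they are not challenged here. 97% power corresponds to z = 1.96 + 1.88 = 3.84. At q = 0.5 with the standard error held fixed, z = 3.84 x 0.775 = 2.98 and power is about 85%. But carry-over also changes the standard error.
- Noise independent between items: the slope variance is multiplied by 12/10, the SE by 1.10, and power is about 78%.
- Noise shared by all items: the variance is multiplied by 7.375/10, the SE by 0.86, and power is about 93%.

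Both ignore random slopes. The result depends on the error structure even after q has been assumed.

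**The case against.** The strongest reply is that the article says several items, not the severity ratings. The section holds obvious candidates for sensible pre-filling, such as milestones, diagnoses and intellectual ability. The past-month recall window and the requirement of a TAND-SQ at all five time points both favour fresh ratings. Which fields open blank is item-level app configuration, which the approved full protocol or an app specification, neither of them shown, may already settle.

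Much of this stands. A reader might infer from the quoted rule that ratings are carried forward and that the trajectories will be flattened. The document does not support that: it never says ratings are pre-filled, and the time budget fits history items alone. A reader might also infer that earlier scores appear beside the scale while the respondent is rating. The article describes the visual summaries only as encouragement to return, so anchoring is plausible but not documented.

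The reply does not dispose of the point. The article did not leave the matter out: it states a data-capture rule and applies it, without limit, to the section that contains the outcome instrument.

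A second reply is that shorter waves protect retention, which the article counts within its most likely challenge. That is a real cost, but it argues for pre-filling history items, not ratings.

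**Conclusion.** The point holds in conditional form. As written, the pre-filling rule covers the outcome section without restricting itself to history items. If any 0-10 rating or question 8.2 item is among the pre-filled ones, untouched values would enter as new measurements, bias slopes toward zero and enlarge the stable class. Under the assumed shares, the mean slope would be 93% of the true slope at q = 0.25 and 78% at q = 0.5. The real size is unknown, because neither the pre-filled items nor the share left untouched is stated. It is nil if the ratings already open blank. No loss of power should be quoted as a result, and the stated power figures are not shown to be wrong. The change is still worth making now, because the data cannot be recovered later and the correction is small.

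**What to change.** - Limit pre-filling in the TAND-SQ to history-type items, for example milestones and diagnoses, and say so in the protocol.
- Have every 0-10 severity rating and every question 8.2 item open blank at each wave, or require an active confirmation of an unchanged value that the app logs.
- Keep earlier scores off the rating screens, and show the updated trend once the wave is submitted. Downloaded PDF summaries mean that earlier answers cannot be hidden completely.
- Check T2 data already collected for untouched values. The soft launch was in December 2025, so at 3-month intervals the first T2 entries could fall around March 2026.

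The cost is an app setting, a few more minutes per wave and a small retention risk. If the ratings already open blank, a sentence saying so, and saying where earlier scores are shown, is enough.

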#### Measures and Data Collection Methods (Aim 3)

The schedule of enrollment, baseline assessment, intervention, and immediate post-, 3-month post-, and 6-month postintervention assessments is shown in Table 4. In addition to data measures for aims 1 and 2, measures for aim 3 were selected to evaluate the feasibility, acceptability, and potential efficacy of the “Well-Beans for Caregivers” intervention. These additional measures include attendance rate as a measure of feasibility, session feedback forms as measures of feasibility and acceptability, completed by session facilitators, observers, and caregiver participants, and 2 measures of family functioning and quality of life. A measure of psychological flexibility, the hypothesized ACT therapeutic mechanism of change, has also been included, namely the Psy-Flex [81]. All clinical measures will be collected via REDCap before the intervention starts (preintervention), immediately post intervention, and at 3 months and 6 months after the intervention occurred. Session feedback forms will be collected from participants, observers, and facilitators after each session.

**Table 4 table4:** Data collected using REDCap (Research Electronic Data Capture) for aim 3.

Measure				Time point		Time to complete
Caregiver demographic information				Preintervention		10 min
**Feasibility and acceptability**						
	Attendance		After each session		N/A^a^	
	Session feedback forms: caregivers, observers, and facilitators		After each session		5-7 min	
**Potential efficacy of intervention**						
	**Psychological flexibility**					
		Psy-Flex [81]	Pre-, immediately post-, 3-month post-, and 6-month postintervention		3-5 min	
	**Caregiver burden**					
		TAND-SQ^b^ question 8.2 [20]	Pre-, immediately post-, 3-month post-, and 6-month postintervention		3 min	
	**Caregiver well-being**					
		Brief Resilience Scale [82] Patient Health Questionnaire-9 [64] Generalized Anxiety Disorder 7-item scale [65] World Health Organization-5 Well-Being Index [83]	Pre-, immediately post-, 3-month post-, and 6-month postintervention		10 min	
	**Family support and quality of life**					
		Multidimensional Scale of Perceived Social Support [66] Family Impact of Childhood Disability Scale [67]	Pre-, immediately post-, 3-month post-, and 6-month postintervention		15 min	

^a^N/A: Not applicable.

^b^TAND-SQ: self-report quantified tuberous sclerosis complex–associated neuropsychiatric disorders checklist.

### Data Analysis

#### Statistical Analysis Plan (Aim 1)

TAND severity will be quantified using the CSS_mean_ for each cluster and the TTSS_mean_/TTSS_max_ for overall TAND severity. These will be used to identify latent TAND severity trajectories using latent class mixed effect modeling [84]. The number of classes will be chosen based on statistical measures of model fit, the stability of the latent profiles, and the group sizes. Multinomial regression modeling [84] will be used to investigate the association of potential subject-specific covariates with the identified latent classes (predictors of TAND severity trajectories). All analyses will be done using R software (R Foundation for Statistical Computing) [85].

Power calculations are based on the estimation of the time trajectory and comparing different latent trajectories. Based on the data from the preliminary data analyses described earlier of 21 repeat TAND-SQs (42 observations), the power calculations were made in 2 ways. First, based on simulations [86] using a single slope (mean profile), power for sample sizes of n=500 and n=300 was calculated at a slope of -1.05% (power=100%/100%) and at –0.5% (power=97%/81%). Second, simulations were generated for n=500 and n=300 using a 3-trajectory solution with change in trajectories set at +1%, 0%, –1% (power=100%/100%), +0.5%, 0%, –0.5% (power=84%/72%), and 0%, +0.5%, +1% (power=86%/83%). Power calculations allowing for 3 different estimated baseline values of TTSS_max_ (75, 100, and 125) in addition to differing slopes for trajectories, show for n=500, 100% power (with 1% change in trajectories) and 93% power (with 0.5% change in trajectories). A sample size of n=300 using similar power calculations shows 100% power for 1% and 77% power for 0.5% differences in trajectory slopes.

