### Potential Challenges and Solutions

The most likely challenge in this study will be the recruitment and retention of 500 participants for the longitudinal data collection for aims 1 and 2. However, the TAND consortium and research team are well placed in the international TSC community to manage this process, and the 4-year track record of the TAND consortium during the TANDem-1 project is a testament to this. We acknowledge that the power calculations for the trajectory analyses were based on preliminary data with only 21 repeat TAND-SQ observations and that the mediation power analysis came from preliminary data with 51 caregivers. These data therefore provide limited justification for the final statistical analysis plan. However, we have taken a very conservative approach to prepare our power calculations. First, we acknowledge that TSC is a rare disease and that these represent the first-ever data of repeat measures on the TAND-SQ and of caregiver well-being on question 8.2. Second, there was a funder requirement for a prospective statistical analysis plan and power calculations. As outlined in the data analysis section of this protocol, we have therefore used different approaches to do power calculations, including the use of simulations and using very conservative parameters for change measurement. We also acknowledge that the intervention pilot is small, with only 30 participants in a quasi-experimental pre-post design with no control group and no formal power calculation. This approach was selected for 2 reasons. First, the primary aim of the pilot trial was to evaluate feasibility and acceptability with a very limited evaluation of efficacy (“signal seeking” of potential future outcome measures through evaluation of effect sizes of change on theoretically motivated measures) as a secondary aim. Second, there was a funder requirement only to allow small pilot studies to be conducted through this funding mechanism.

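### The aim 1 power of 84–100% at n=500 does not measure identification of three latent trajectories, which the planned analysis would rarely achieve under the same scenarios

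*Protocol article*

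**What the plan says.** The aim 1 hypothesis reads: "We hypothesize that longitudinal analysis of TAND severity data will identify at least 3 differential trajectories", named as stable, worsening and improving. Under Statistical Analysis Plan (Aim 1), severity scores go into a latent class model: "These will be used to identify latent TAND severity trajectories using latent class mixed effect modeling". The number of classes is left to the data: "The number of classes will be chosen based on statistical measures of model fit, the stability of the latent profiles, and the group sizes".

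The same section introduces the power as follows: "Power calculations are based on the estimation of the time trajectory and comparing different latent trajectories". For the trajectory comparison, "simulations were generated for n=500 and n=300 using a 3-trajectory solution with change in trajectories set at" three sets of slopes. Power is given for n=500 and n=300 in that order:

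- Single slope: 100%/100% at −1.05% per month and 97%/81% at −0.5%.
- Three trajectories: 100%/100% for +1/0/−1%, 84%/72% for +0.5/0/−0.5%, and 86%/83% for 0/+0.5/+1%.
- Three trajectories with baselines 75, 100 and 125: 100%/100% at 1% and 93%/77% at 0.5%.

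No residual or random-effect SD, class shares, test or treatment of class membership is given. Potential Challenges and Solutions concedes that the pilot data are thin, then says "we have taken a very conservative approach to prepare our power calculations".

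**The concern.** Comparing slopes between trajectories and discovering that trajectories exist are different tasks. The first can have high power when the second has almost none, because a group mean slope is estimated from well over a hundred people while a class has to be recognised from individual curves. The hypothesis needs the second task; the stated power describes the first.

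Much of the study depends on the classes. The multinomial regression for predictors uses them as its outcome, and the trajectory mediation in aim 2 uses them again. If classes as far apart as those in the power scenarios cannot be recovered, a one-class result says little about the hypothesis. A reader who sets it against 84–100% power would take it as evidence against three trajectories.

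**Working it through.** **Inputs.** Visits are at 0, 3, 6, 9 and 12 months, so the sum of squared deviations in time is 36+9+0+9+36 = 90. Baseline TTSS_max has mean 100.5 and SD 64.2 (Introduction, preliminary data), so 1% is about 1 point. Assumed because not stated: two-sided 5% tests, normal scores, no dropout.

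**Step 1: noise implied by the protocol's own power.** The single-slope entry is "0.5% (power=97%/81" percent. Power = Φ(b√n/s − 1.96), where s is the SD of one person's estimated slope.

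- n=500, 97%: 1.96 + 1.88 = 3.84; s = 0.5 × √500 / 3.84 = 2.91 points/month; residual SD = 2.91 × √90 = 27.6.
- n=300, 81%: 1.96 + 0.88 = 2.84; s = 0.5 × √300 / 2.84 = 3.05; residual SD = 3.05 × √90 = 29.0.

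The two agree on about 28. The pilot is in the same range: 5 of 21 (24%) stayed within 10 points, with a mean change near −10. That fits a residual SD of about 22, and an SD of 28 would give 19% (4 of 21). With residual SD 28, the between-person SD is √(64.2² − 28²) ≈ 58.

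**Step 2: slope comparison if membership were known, equal thirds.** The 2-df noncentrality is (n/3) × Σ(slope deviation)² / s². At n=500, slopes ±0.5 and s=2.91 it is 166.7 × 0.5 / 8.47 = 9.8, so power is 81%. A test of the two extreme groups gives 88%.

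| Scenario | Stated | Known groups, s = 2.91–3.05 |
|---|---|---|
| ±1%, n=500 | 100% | 100% |
| ±0.5%, n=500 | 84% | 77–81% (2 df), 85–88% (extremes) |
| 0/+0.5/+1%, n=500 | 86% | the same |
| ±0.5%, n=300 | 72% | 53–58% (2 df), 64–68% (extremes) |
| 0/+0.5/+1%, n=300 | 83% | the same |

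The n=500 figures are similar to a known-membership comparison. The n=300 figures are not.

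**Step 3: separation between classes.** Adjacent classes are 0.5 or 1 point/month apart, against s of about 2.9, which is 0.17 or 0.34 SD. With three equal classes and every parameter known, classification by slope is right for (4Φ(d/2) − 1)/3 of people, where d is that separation: 38% at 0.5% and 42% at 1%. Chance is 33%. Adding baselines of 75/100/125 to the 1% slopes raises it to 46% (simulated).

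**Step 4: the planned type of analysis.** I simulated 200 studies per scenario with n=500, intercept SD 58, residual SD 28 and no extra random slope. A random-intercept latent class model with class-specific intercepts and slopes was fitted for 1–4 classes.

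| Truth (shares) | BIC: 1 class | BIC: 3 | SABIC: 3 | AIC: 3 |
|---|---|---|---|---|
| ±1% (equal) | 100% | 0% | 0% | 8% |
| ±1% (24/24/52) | 100% | 0% | 1% | 4% |
| ±0.5% (equal) | 100% | 0% | 0% | 3.5% |
| ±0.5% (24/24/52) | 100% | 0% | 1% | 4% |
| 0/+0.5/+1% (equal) | 100% | 0% | 0% | 3.5% |
| ±1%, baselines 75/100/125 (equal) | 98% | 0% | 0.5% | 8% |
| ±1%, same baselines (24/24/52) | 98.5% | 0.5% | 1% | 7% |
| ±0.5%, same baselines (equal) | 100% | 0% | 1.5% | 7.5% |
| One true class | 100% | 0% | 0% | 2.5% |

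The hypothesis says at least three. Adding the four-class selections takes AIC to 5–12.5%, against 3.5% when there is only one class; BIC is unchanged. A separate run of 30 studies in each of three scenarios gave BIC 0/30 and AIC 1–4 of 30 (3–13%).

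**Step 5: sensitivity to the assumed noise** (±1%, equal shares, same baseline, BIC).

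- Residual SD 14: one class in 56%, two in 44%, three in 0%.
- Residual SD 10: two classes in 30/30.
- Residual SD 7: two classes in 100%.
- Residual SD 3: three classes in 100%.

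Cutting the between-person SD to 30 (residual SD 28, baselines 75/100/125) left three classes at 0%.

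**The case against.** The protocol does not claim a probability of finding three classes. It ties its power to slope estimation and to comparing trajectories, and Unexpected Results accepts that more or fewer than three may appear. It also admits that 21 repeat checklists are limited justification. All of that stands. But the comparison figures are the only support offered for the sample size in aim 1, and neither Unexpected Results nor the admission about the pilot addresses whether classes this close could be recovered.

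A reader might infer that the sponsor simulated with class membership known. The n=500 figures suggest it, but the protocol does not say so. The n=300 values of 72% and 83% exceed what such a test gives. With equal shares, those two scenarios have the same slope contrasts, so a test of equal slopes could not return both. The 93% with differing baselines is only bracketed, at about 76–97% depending on test and layout. The provenance of the figures is therefore open.

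A reader might also infer that the study will return one class, or that three trajectories cannot be found at all. That goes too far. The result belongs to the stated slopes and to normal scores. In small runs of 10 studies each, BIC chose two classes in 10/10 at ±3 points/month and three in 10/10 at ±8. Nor do the documents support a claim that a skewed score would create false classes, since they give no distribution for it.

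Finally, the protocol names no fit criterion and adds stability and group size. AIC is the most generous of the three tried and still rarely reaches three classes.

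**Conclusion.** The point holds in this form: the 84–100% power at n=500 is not power for the aim 1 hypothesis. Under the protocol's own scenarios, the probability of selecting three classes is about 0–0.5% by BIC and roughly 3–13% by AIC. This rests on a residual SD of about 28 inferred from the single-slope power, normal scores, a random-intercept model and no dropout. The noise assumption does not decide the matter: with ±1% slopes and a shared baseline, BIC still does not reach three classes at residual SD 14, 10 or 7. True random slopes or dropout would make recovery harder. How the stated figures were produced cannot be settled from the document.

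**What to change.** In Statistical Analysis Plan (Aim 1):

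- Label the existing three-trajectory figures as power to compare slopes between trajectories. State the test and how membership was treated, and say that they are not the probability of identifying three classes.
- Add a simulation of the planned pipeline: fit one to four classes and select by the stated criteria, with variance components and class shares given. Report the probability of selecting three classes and the smallest separation recoverable with 500 people at five visits.

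In Potential Challenges and Solutions, remove the description of the power parameters as very conservative, or limit it to the slope sizes. Note there or under Unexpected Results that a one-class result at these separations would not refute the hypothesis.

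The cost is a few days of simulation and a less favourable stated power. No extra participants are needed.
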